### Intervention

Both groups are offered standard diabetes therapy, as they should not experience
any deficiency in professional care. All participants are encouraged to measure
blood glucose (BG) ideally before meals, two hours after meals, and before going
to bed, but at least three times a day during the entire study. The customer
service for telephone support will be available at any time.

#### Control group

An exclusion of the CG from using the DHA is necessary, but it is not
possible to monitor the use of other digital tools for diabetes
self-management. Therefore, it will be advised not to use any assisting
digital programs during the study. By finishing the trial, every patient
will be invited and guided to use the DHA.

#### Intervention group

The IG will apply a DHA, named ESYSTA®. The patients will be taught to use
both components, app and portal, which automatically synchronize with each
other. The DHA system is supposed to replace a paper-based diabetes
diary.

By using a compatible blood glucose meter (BGM) and/or insulin pen, patients
can import BG or insulin data by connecting with the app via Bluetooth®. The
system enables the connection of BGMs that are compatible with the “Glucose
Profile” standard in Version 1.0 of the “Bluetooth® Special Interest Group.”
This standard uses “Bluetooth® Low Energy” as transmission technology. A
list of compatible devices is provided to the participants.^
17
^ It is also possible to document values manually and even when the app
is offline.

The app offers a detailed daily display as well as a daily BG history (3-day
or 7-day view) so patients can review their daily routine for themselves. A
target range analysis and a traffic light provide quick information about
the metabolic setting to increase motivation (Figure 3).

**Figure 3. fig3-19322968221075333:**
[figure not shown]
User interface of the app.^
18
^

In the portal, more detailed graphics and tables than in the app are
available (Figure 4). The traffic light system is also used here, for example, in a
table to monitor hypoglycemia or hyperglycemia, measurements per day, and
other points of interest. In addition, critical values and incorrect dosing
can be quickly detected with graphics for insulin and BG. Both patient and
doctor have access to the portal. Moreover, HCPs can import data from the
portal into their practice or hospital IT system to avoid data loss or
transmission errors. A protected exchange of messages between patient and
physician through an integrated e-mail system is also possible via the
portal (in addition to routine appointments and telephone consultations).
Health care professionals are instructed to use the portal during the study
as part of the intervention.

**Figure 4. fig4-19322968221075333:**
[figure not shown]
User interface of the portal.^
19
^

Patients in the IG will be provided a BGM compatible with the DHA, which they
may keep after closure of the trial. Those patients who already own a
compatible device have the option to use their current BGM for the study. If
needed, the participants will also receive a kit with standard lancing
device, single-use lancets, box of test strips, and compatible insulin
pens.

### Measures and Questionnaires

Primary endpoint of the study is the change of HbA1c during the use of the DHA.
The main hypotheses are listed in Table 2. Measurement of the HbA1c
value, blood pressure, waist circumference as well as weighing and pregnancy
test will take place in every visit in both groups. Blood samples will be tested
in the local laboratory of each study site.

**Table 2. table2-19322968221075333:** Hypotheses of the Clinical Trial.

Hypothesis	Indicator	Relation
H0	Any	Is having no effect
H1	HbA1c	Is superior and has a clinical meaningful^ a ^ impact on lowering the HbA1c compared with standard diabetes care
H2	Hypoglycemic events	Is superior and has an impact on lowering hypoglycemic events compared with standard diabetes care
H3	Self-management	Is superior and improving self-management of diabetes patients compared with standard diabetes care
H4	Mental health	Is superior and reduces symptoms that represent a risk potential for secondary diseases such as depression compared with standard diabetes care

a HbA1c difference of 0.3 HbA1c % points.^20,21^

There will be several patient-reported outcome (PRO)^22-25^ questionnaires for
evaluating changes in empowerment, self-management, mental health, quality of
life, and other outcomes. The first questionnaire on personal data, medical
history, and inclusion criteria as well as all further questionnaires will be
completed via paper pencil.

All endpoints with matching questionnaires are listed and explained in Table 3.

**Table 3. table3-19322968221075333:** Predefined Endpoints.

Hypothesis	Primary endpoint	Data collection/questionnaire
H1	Change of HbA1c during the use of DHA	Data from HbA1c testing at the visit
Hypotheses	Secondary endpoints	Data collection/questionnaires
H1	Proportion of patients reaching their HbA1c treatment goals <7.0% during the use of DHA	Data from HbA1c testing at the visit
	Proportion of patients reaching their HbA1c treatment goals <6.5% during the use of DHA	
	Achieving a higher proportion of patients reaching the HbA1c treatment goals compared with CG	
H2	Frequency of severe and nonsevere hypoglycemic episodes (ADA recommendations: <70 mg/dL risk of hypoglycemic episodes, <54 mg/dL clinically important hypoglycemic episodes^ 26 ^)	Data from patient’s recollections (using DHA or Diary)
	Frequency of severe hyperglycemic events (ketoacidosis/nonketotic hyperosmolar coma)	Data from patient’s recollections (using DHA or Diary)
H3 H4	Changes in motivation and patient self-management	Measured by daily conducted BG values (DHA or Diary) and questionnaires:SDSCA^ 27 ^ collects data on self-management (including diet, exercise, blood sugar testing, smoking, foot care, and intake of medications) DES-SF^ 28 ^ measures empowerment and attitudes toward diabetes EQ-5D-5L^ 29 ^ captures health-related quality of life (including mobility, self-care, usual activities, pain/discomfort, anxiety/mental health) WHO5^ 30 ^ capturing the subjective well-being CESD-R^ 31 ^ gives hints for depression PAID^ 32 ^ discloses problems/dissatisfaction in diabetes treatment
	Patients with either beneficial or nonexistent effect(s), that is, patient groups, who achieve larger or smaller HbA1c changes associated with the use of DHA	HbA1c testing at visit and questionnaires: SDSCA DES-SF
	Reduction in the number of high and low blood sugar readings	Data from DHA or Diary using the following cutoff values/ranges: 80-130 mg/dL (fasting or preprandial)^ 26 ^
	Termination rate(s)	Data from DHA and QV1, QV2, QV3 to collect data on patients’ experience and SMBG compliance (one questionnaire for each visit)
H3	Usability for patients in daily self-management	SDSCA UEQ^ 33 ^ to capture the user experience
	Number of preprandial and postprandial testing events	Data from DHA or Diary
	Usability and overall satisfaction of patients and HCPs with DHA	CRF (self-made) to assemble all problems with DHA TVQ (self-made) to check the correct handling of SMBG within the telephone call HCP (self-made) shows the evaluation of the physicians’ and also patients’ overall satisfaction with DHA UEQ

Abbreviations: ADA, American Diabetes Association; BG, blood glucose;
CESD-R, Center for Epidemilogic Studies Depression Scale - Revised;
CG, control group; CRF, case report form; DES-SF, Diabetes
Empowerment Scale–Short Form; DHA, digital health application;
EQ-5D-5L, Questionnaire of the EuroQol Group in 5-level-version;
HCPs, health care professionals; PAID, Problem Areas in Diabetes
Scale; QV, Questionnaire for Visit 1/2/3; SDSCA, Summary of Diabetes
Self-care Activities Measure; SMBG, self-monitoring of blood
glucose; TVQ, Telephone Visit Questionnaire; UEQ, user experience
questionnaire; WHO5, Questionnaire of WHO Collaboration Centrein
Mental Health.

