### Statistical Analyses

An overview of statistical methods is given here, which can be adapted depending
on the data situation at the end of the study.

First of all, a summary of baseline data (eg, laboratory and anamnestic data) is
essential. Including the 95% confidence interval, categorical variables are
presented in absolute and relative frequencies and continuous variables are
described by the number of participants, mean, standard deviation, standard
error, median, minimum, and maximum.

Parametric and nonparametric tests will be used to compare quantitative variables
and frequency, and the chi-square test is applied on qualitative variables.
Furthermore the Kolmogorov-Smirnov test will be applied as a test of normal
distribution.

We expect the changes in HbA1c value in this study to follow a normal
distribution (based on previous other studies).^
34
^

Analysis of variance (ANOVA) is the main statistical method to analyze the effect
of the DHA on HbA1c as primary endpoint to show whether there is a significant
difference in primary outcomes between the two treatment groups.^
35
^ Data from both Visit 2 and Visit 3 will be compared with baseline data
from Visit 1. In addition, an ANOVA with repeated measures is performed, and
differences between participants as well as the number of visits and a possible
interaction between treatment and number of visits are represented by the linear
model.

Assuming a significance level of .05, ANOVA can be used to check whether the null
hypothesis can be rejected and which alternative hypotheses (Table 2) can be
accepted. Possible correlations are determined using the Pearson correlation
coefficient.

For multiple imputation of missing data, the jump-to-reference (J2R) method is
used, among others. To impute missing single HbA1c values, data from the
patient’s file of the treating HCP can be used as a substitute (as well as from
DHA of the IG). If no values are available here, the “Last mean carried forward”
method can be used.^
36
^

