#### Sample size calculation

The sample size calculation is performed with the program G*Power.^37,38^ It is
assumed that a reduction of 0.4 HbA1c % points (reduction from 8.0 to 7.6)
and an HbA1c standard deviation from 0.8 in the CG and 1.0 in the IG are
present. This assumption is based on the previous results of the analysis of
the AOK START (Systematic Trial with Analysis of Results in Telemedicine)
Project.^10,39^ This resulted in an effect size of 0.6625 and a
power of 0.95. With this assumption, a sample size of 77 participants in
each group (total of 154; dropout already included) will be necessary to
show a significant effect. A 20% drop-out rate is estimated based on the
experience of a previous study.^
34
^

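### H1 claims a clinically meaningful effect of 0.3 HbA1c points, but the stated acceptance rule tests only against zero

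*Protocol article*

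**What the plan says.** Table 2 (Measures and Questionnaires) gives H0 as "Is having no effect". H1, for HbA1c, reads "Is superior and has a clinical meaningful", and the comparator is standard care. Footnote a defines clinically meaningful as an "HbA1c difference of 0.3 HbA1c % points".

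Statistical Analyses names ANOVA as the main method; what it looks for is a "difference in primary outcomes between the two treatment groups". The decision rule follows. With alpha at .05, the ANOVA settles both rejection of the null and acceptance of the alternatives; the key words are "hypothesis can be rejected and which alternative hypotheses (Table 2) can be". The 0.3 figure does not appear in that section or in the sample size calculation.

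The sample size section gives the planning values: a fall of 0.4 points, from 8.0 to 7.6, with SDs of 0.8 for the control group and 1.0 for the intervention group. It also states an effect size of 0.6625, power 0.95, 77 per group with dropout included, and 20% dropout.

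**The concern.** H1 makes two claims: that the app is superior, and that its effect is clinically meaningful. The only null that is stated, and the only test tied to accepting H1, concern a zero difference. Rejecting a zero effect supports superiority and says nothing about clinical relevance. A true difference of, say, 0.2 fits neither H0 nor H1, yet rejecting H0 is the written route to accepting H1.

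The article says that the results are to support certification of the app as a prescribable digital health application in Germany. A headline conclusion of clinical relevance would then rest on a test that cannot establish it.

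**Working it through.** **Inputs.** From the sample size section: assumed difference 0.4, SDs 0.8 and 1.0, effect size 0.6625, power 0.95, 77 per group, 20% dropout. From Statistical Analyses: alpha .05. From Table 2: threshold 0.3.

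**1. Reproduce the plan's figure.** A two-sample t test against zero with d = 0.6625, two-sided alpha .05 and power 0.95 needs 61 per arm. Then 61/0.8 = 76.25, rounded up to 77, as stated. A one-sided test gives 51, then 64, and does not match. So the trial is sized for a two-sided test against zero, and 0.3 plays no part. (0.6625 does not follow from 0.4 and the stated SDs, which give 0.4/0.9055 = 0.442. That is a separate matter, and the steps below do not use 0.6625.)

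**2. Smallest significant difference.** Pooled SD = √((0.8² + 1.0²)/2) = 0.9055. The smallest difference reaching p < .05 is t(.975, 2n−2) × SD × √(2/n). I use n = 61 (completers only) and n = 77 (all randomised; planned imputation could keep the analysed number near this).

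| SD | n = 61 | n = 77 |
|---|---|---|
| 0.9055 (stated SDs) | 0.325 | 0.288 |
| 0.70 (assumption) | 0.251 | 0.223 |

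The 0.70 is not in the article. It is what a change score would have with a baseline to follow-up correlation of 0.7 and equal SDs at both times: 0.9055 × √(2 × (1 − 0.7)) = 0.70. A significant estimate below 0.3 becomes possible once the SD falls below about 0.84 (n = 61) or 0.94 (n = 77).

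**3. Chance of a significant estimate below 0.3, true difference 0.2.** The standard error is SE = SD × √(2/n), and the estimate is treated as normal with the SD fixed.
- SD 0.9055, n = 61: the smallest significant difference (0.325) is already above 0.3, so the chance is 0.
- SD 0.9055, n = 77: SE = 0.146; Φ((0.3 − 0.2)/0.146) − Φ((0.288 − 0.2)/0.146) ≈ 2.6%.
- SD 0.70, n = 61: SE = 0.127; about 13%.
- SD 0.70, n = 77: SE = 0.113; about 23%.

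Simulation with the SD estimated in each trial gives 0.3% and 3.4% at the stated SDs, so about 0 to 3% is a fair summary.

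**4. Chance of any significant result, true difference 0.2** (noncentral t). SD 0.9055: 22.7% (n = 61) and 27.5% (n = 77). SD 0.70: 34.7% and 42.1%. Read literally, the acceptance rule would allow H1 to be accepted in each of these trials.

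**5. What a significant estimate excludes.** At n = 61 and SD 0.9055 the 95% CI half-width is 0.325. An estimate of 0.33 has a CI of 0.33 ± 0.325, about 0.01 to 0.65. For the lower limit to exceed 0.3, the observed difference must exceed 0.3 + 0.325 = 0.625 (n = 61) or 0.3 + 0.288 = 0.588 (n = 77).

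**6. Would a formal test against 0.3 be feasible?** With a true difference of 0.4 and SD 0.9055, its power is 8.8% (n = 61) to 10.0% (n = 77). It is out of reach at this sample size.

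**The case against.** Testing superiority against zero while citing a relevance threshold is common practice. The analysis section calls itself an overview that may be adapted and says only that ANOVA can be used for this check. One can fairly read it as letting the test settle superiority, with the estimate then compared with the footnote. How that comparison is made is often left to a full protocol or SAP, which is not shown here.

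Part of this stands. A reader might infer that the plan will routinely label significant differences below 0.3 as clinically meaningful. The documents do not support that. The article never says it will do so, and at its own SDs such results are rare (step 3). They become frequent only with an SD near 0.70, which is an assumption. Nor is 23 to 28% the chance of a significant estimate below 0.3. It is the chance of any significant result at a true 0.2, and at the stated SDs most of those estimates lie at or above 0.3. A further inference, that the F-test leaves the direction open, adds little: H1 specifies lowering of HbA1c, and reading the sign after a two-sided test is standard.

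What does not stand is that this is only omitted detail. The article states an acceptance rule, and that rule does not match the hypothesis it is meant to accept.

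**Conclusion.** The mismatch is real and lies in the stated text: H1 carries a 0.3 threshold, H0 is zero, and rejecting H0 is the written route to H1. At the stated SDs, the main consequence is not significant estimates below 0.3 (about 0 to 3% of trials; about 13 to 23% at a true 0.2 if the SD is 0.70). It is that a significant result, even with an estimate above 0.3, leaves near-zero effects within the confidence interval. If the true difference is 0.2, some 23 to 28% of trials would be significant and could be accepted under H1.

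These figures assume a two-sided .05 comparison of two means, 61 to 77 analysed per arm, and that the stated SDs apply to the analysed outcome. The superiority test itself remains valid. Only the clinical relevance claim attached to it does not follow.

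**What to change.** - Limit the tested H1 in Table 2 to superiority: two-sided .05, with the estimate favouring the intervention group.
- Judge clinical relevance separately, by reporting the between-arm difference and its 95% CI against 0.3.
- Make no claim of a clinically meaningful effect if the estimate is below 0.3. If the CI includes values below 0.3, say so in the conclusion.
- Amend the acceptance sentence in Statistical Analyses to match.

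At the stated SDs the point-estimate condition alone changes few conclusions. The CI statement carries most of the correction, so both are needed.

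The cost is wording. Design and sample size do not change, and no formal test against 0.3 is needed. The downside is that a significant result may support superiority only. At a true difference of 0.4 and SD 0.9055, the chance of significance together with an estimate of at least 0.3 is about 68% at 61 per arm, the same as for significance alone, and about 75% against 78% at 77 per arm.

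### Hypoglycaemia, glucose-reading and testing counts come from the app in one arm and a diary in the other, so arm differences mix glycaemia with how much is tested and recorded

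*Protocol article*

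**What the plan says.** Table 2 of the protocol article states H2 as a between-arm claim: the DHA "Is superior and has an impact on lowering hypoglycemic events compared with standard diabetes care". Table 3 gives the endpoint as "Frequency of severe and nonsevere hypoglycemic episodes (ADA recommendations: <70 mg/dL risk of hypoglycemic episodes", with a second cut-off at 54 mg/dL, and names the source as patients' "recollections (using DHA or Diary").

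Two further rows of Table 3 use DHA or diary as their source. In the H3/H4 block stands "Reduction in the number of high and low blood sugar readings"; under H3 stands "Number of preprandial and postprandial testing events".

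The Control group section excludes that arm from the DHA. The Intervention group section says the DHA is meant to take the place of the paper diary and that patients "can import BG or insulin data by connecting with the app via Bluetooth"; it also allows manual entry. It provides intervention patients with a compatible meter unless they already own one. No meter supply is stated for controls. Under Intervention, both arms are asked to measure "blood glucose (BG) ideally before meals, two hours after meals, and before going" to bed, and at least three times a day.

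The Statistical Analyses section uses ANOVA to decide which Table 2 hypotheses can be accepted. It mentions no allowance for the number of tests.

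**The concern.** Since controls cannot use the DHA, their share of the DHA-or-diary data can only come from a diary. The recording medium therefore follows the randomised arm.

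That matters because nonsevere hypoglycaemia here is defined by glucose cut-offs. A low value exists in the data only if the patient tested at that moment and the result was recorded. The DHA is expected to change testing, and it may also make recording more complete. A raw count can then differ between arms although glycaemia does not.

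On H2, a real reduction could be hidden or an apparent excess of hypoglycaemia could appear under the DHA. On the testing count the error runs the other way: more complete recording would look like better self-monitoring.

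**Working it through.** The protocol gives no design figure for H2 or for the reading and testing counts, so there is none to reproduce. Its sample size serves only to set the number per arm. An effect size of 0.6625, two-sided alpha 0.05 and power 0.95 need 61 per group by t-test, and 61/0.8 = 76.25, rounded up to the stated 77 with 20% dropout.

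**Inputs from the protocol.** Follow-up is at least 180 days. Testing ranges from 3 a day (the floor) to about 7 a day (3 before meals, 3 after meals, 1 at bedtime, assuming three meals).

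**Assumed inputs, not in the protocol.** The share of diary readings captured is 70% to 100%; the intervention group records everything; omissions do not depend on the glucose value.

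**Formula.** Expected recorded lows per patient = tests per day × days × probability that a reading is low × share recorded. With equal glycaemia the probability and the days cancel:

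ratio (IG/CG) = (IG tests × IG share) / (CG tests × CG share).

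| Testing, IG vs CG | Share recorded, IG vs CG | Ratio |
|---|---|---|
| equal | equal | 1.00 |
| equal | 1 vs 0.9 | 1/0.9 = 1.11 |
| equal | 1 vs 0.8 | 1/0.8 = 1.25 |
| equal | 1 vs 0.7 | 1/0.7 = 1.43 |
| IG 20% more | 1 vs 0.8 | 1.2/0.8 = 1.50 |
| 4 vs 3 a day | equal | 4/3 = 1.33 |
| 4 vs 3 a day | 1 vs 0.8 | 4/(3 × 0.8) = 1.67 |
| 7 vs 3 a day | equal | 1,260/540 = 2.33 |

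The last row is the edge of what the testing instruction allows, not an expectation. The same ratios apply to the count of recorded tests. If controls recorded more than the intervention group, the ratio would fall below 1.

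**Effect on a test of raw counts.** This was simulated with gamma-Poisson counts, 61 per arm, 3% of readings low, between-patient variance 1 to 2, a Mann-Whitney test and 4,000 runs, all of these being assumptions. With equal true glycaemia, the intervention arm is falsely found worse in about 2% of trials at ratio 1.00, 9–18% at 1.25, 13–26% at 1.33 and 33–64% at 1.67. Dividing by recorded tests brings total type I error back to about 5–6%.

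**Effect on a true benefit.** With a true 30% reduction, the expected count ratio is 0.7 × 1.33 = 0.93 at 4 vs 3 tests a day, and 0.7 × 1.67 = 1.17 if diaries also capture only 80%. Simulated power to show the benefit (variance 1) falls from about 36% with equal testing to about 5% and under 1% respectively.

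**Limit of the per-reading rate.** Suppose controls write down every low but only 80% of other values, with 3% of readings low. The recorded-low ratio is then 1.00, but the control rate per recorded reading is 0.03/(0.03 + 0.8 × 0.97) = 0.03/0.806. The IG/CG rate ratio becomes 0.806, an apparent benefit with no change in glycaemia. A denominator corrects testing intensity but not selective recording.

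**The case against.** Several replies have force.

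- Both arms receive the same testing instruction with the same floor. A reader might infer that H2 compares recording methods instead of glycaemia; the text does not support that. The comparison mixes the two, and the bias is zero if testing and recording are equal.
- Severe hypoglycaemia and ketoacidosis or coma are clinical events that do not scale with the number of tests. They do share the recollection source.
- Intervention data are not purely automatic, because manual entry is allowed and H2 rests on recollection in both arms.
- That H2 is a raw count is an inference: the endpoint is a frequency without a stated denominator, and a denominator or offset is ordinary content for an analysis plan that is not shown. Only the readings and testing rows are worded as numbers.
- A reader might object that post-meal and bedtime values would be counted as high. The row reads "Data from DHA or Diary using the following cutoff values/ranges: 80-130 mg/dL (fasting or preprandial"), which already ties the range to fasting or preprandial values.
- A reader might conclude that H3 is uninterpretable. It is not: SDSCA covers blood sugar testing on paper in both arms, and QV1–QV3 collect compliance with self-monitoring.
- The capture rates are assumptions. If patients skip routine values but note lows, the ratio for lows is nearer 1.

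These points narrow the concern. They do not remove it, because the data source is fixed in Table 3 and differs by arm. An analysis plan can add a denominator but cannot recover readings that were never recorded.

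**Conclusion.** The point holds for nonsevere hypoglycaemia (H2), the number of high and low readings (H3/H4) and the number of testing events (H3). Raw between-arm differences in these mix glycaemia with testing and recording intensity.

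Under equal glycaemia the distortion is none with equal testing and recording, 1.25-fold at 80% diary capture, and 1.5-fold with 20% more testing as well. No document figure says where in that range the trial will fall. If the app arm tests and records more, as seems likely, raw counts work against the DHA on H2, so this is not an evident route to false superiority there; they flatter it on testing counts.

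Only secondary endpoints are affected, and the HbA1c endpoint is untouched. The change is still worth making because H2 is a named superiority hypothesis.

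**What to change.** 1. In Table 3, collect hypoglycaemic episodes, including severe ones, with the same paper visit-questionnaire item in both arms. QV1–QV3 already exist, so the cost is one item per visit.
2. Analyse low and high values per recorded reading instead of as raw numbers, for example by negative binomial regression with the log number of readings as offset. This needs only wording in the analysis plan.
3. Use the SDSCA blood-sugar-testing items as the arm-neutral measure of self-monitoring.
4. Where the meter allows it, read out its memory in both arms. This is optional, since no meter supply is stated for controls and some data would be missing.
5. Label the remaining DHA-versus-diary counts descriptive and base no H2 superiority claim on them.

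The cost in information is that questionnaire recall is coarser than logged readings. The per-reading rate also leaves selective diary recording and symptom-driven testing uncorrected, which is why it should support the H2 conclusion and not carry it.

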## Methods

### Trial Design

A prospective, multicentric, randomized controlled trial (RCT) will be conducted
over a period of 6 months to investigate the effect of a DHA on HbA1c levels in
patients with type 1 and type 2 diabetes mellitus. To this end, we will compare
two groups of patients fulfilling the inclusion criteria (see Table 1): The control
group (CG) will only receive the standard diabetes care and the intervention
group (IG) will additionally use the DHA to monitor diabetes-relevant values
using various graphs and observe potential changes in these endpoints. Each
group will consist of at least 77 patients and will be supervised for a minimum
of 180 days. The schematic design of the DAVOS trial (E**V**aluation
**O**f the Impact of E**S**ysta on Hba1c in Patients with
Type 1 and Type 2 Diabetes mellitus in **DA**ily practice) is shown in
Figure 1.

**Table 1. table1-19322968221075333:** Inclusion and Exclusion Criteria in the DAVOS Trial.

*Inclusion criteria*
• Diabetes mellitus type 1 or 2 • ≥18 years old • Treated with insulin • HbA1c at baseline ≥7.5% and ≤11.0% • Not having used the investigated DHA in the past 12 months • Willing to use a smart glucometer and/or smart insulin pen • Internet access, smartphone/computer compatible with the DHA • Digital literacy to use a smartphone adequately
*Exclusion criteria*
• Using other apps linked to a BG meter or using an insulin pump or continuous glucose monitoring • Having used the investigated DHA in the past 12 months • <18 years old • Impairments (also mental impairments, eg, psychotic disorders) • Patients with home nursing (assisting BG testing) • Current participation in a weight loss program • Current participation in another study • Steroid therapy within the past three months (no exclusion criterion if used topically or inhaled less than five times a week) • Blood pressure ≥200 mm Hg at screening • BMI ≥40 kg/m² • Anemia (according to the WHO definition^ 15 ^) • GFR ≤40 mL/min • Current or planned pregnancy, breastfeeding women • Alcohol or drug abuse (within the past three months) • Employees of Emperra GmbH E-Health Technologies (or other institutions being involved in the trial)

Abbreviations: BG, blood glucose; BMI, body mass index; DHA, digital
health application; GFR, glomerular filtration rate; WHO, World
Health Organization.

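### A Table 3 secondary endpoint equates app effect with observed HbA1c change; it should be a between-arm difference in effect across baseline characteristics, reported as exploratory

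*Protocol article*

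**What the plan says.** Table 3 (Predefined Endpoints) includes a secondary endpoint on patients in whom the effect is favourable or absent. An explanatory clause in the same row says who they are: "patient groups, who achieve larger or smaller HbA1c changes associated with the use of DHA". The data column reads "HbA1c testing at visit and questionnaires: SDSCA DES-SF". The row names no comparator. Another row of the table does: "Achieving a higher proportion of patients reaching the HbA1c treatment goals compared with CG".

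The Statistical Analyses section presents itself as an overview that may be adapted to the data. Its main method for the primary endpoint is an ANOVA between the two arms. It adds a repeated-measures ANOVA in which differences between participants and a possible "interaction between treatment and number of visits are represented by the linear" model. No term lets the treatment effect vary with a baseline characteristic. The section also says "Possible correlations are determined using the Pearson correlation" coefficient, without naming variables, endpoint or arm.

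Two further facts matter. Table 1 admits patients with "HbA1c at baseline ≥7.5% and ≤11.0"%, so they are selected on the outcome variable. And Measures and Questionnaires has HbA1c measured at every visit in both groups, so the control data exist.

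**The concern.** The effect of the app in a group of patients is the mean change of its intervention patients minus the mean change of its control patients. The row puts observed change in place of that difference. A patient's change also reflects regression to the mean after selection on HbA1c, visit-to-visit variation, prognosis, standard care and taking part in a study. Both arms receive standard care, and both are encouraged to test at least three times a day.

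Read literally, the endpoint produces groups that benefit and groups that do not, whether or not the app's effect differs between patients. The results are meant to support certification of the app, so a published statement of who benefits would carry weight even as a secondary result.

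**Working it through.** **1. The plan's own figure.** The article gives no figure for this endpoint. The relevant stated figure is the number of patients. The sample size section says "This resulted in an effect size of 0.6625", with power 0.95 and 20% dropout; the analysis section says "Assuming a significance level of .05". A two-sided two-sample t-test with d = 0.6625 needs 61 per group, and 61 / 0.8 = 76.25, rounded up to 77. The stated 77 reproduces. Only the 61 completers and 77 randomised per arm are used below. (0.4 / 0.9055 is 0.44, not 0.6625, but that is a separate matter and does not enter here.)

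**2. What observed change shows when the effect is the same in everyone.** Assumptions, not stated in the documents for this population: HbA1c is normal before selection with mean m = 8.0 or 8.5 and SD 0.9 (close to the 0.8 and 1.0 in the sample size section), and baseline-to-follow-up correlation r is 0.5 to 0.8. Entry is cut to 7.5-11.0% as in Table 1. Every patient gains exactly 0.4, the planned effect.

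Expected change at baseline x is −(1 − r)(x − m) − 0.4. The gap in change between the top and bottom baseline thirds is therefore (1 − r) × (mean of top third − mean of bottom third). The 0.4 cancels.

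| m | Bottom third mean | Top third mean | Gap, r = 0.5 | Gap, r = 0.8 |
|---|---|---|---|---|
| 8.0 | 7.79 | 9.17 | 0.5 × 1.38 = 0.69 | 0.2 × 1.38 = 0.28 |
| 8.5 | 7.95 | 9.55 | 0.5 × 1.60 = 0.80 | 0.2 × 1.60 = 0.32 |

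Simulation with two million patients per setting gives the same gaps, and in addition:

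- With the uniform 0.4 effect, 53-60% of patients fall by at least 0.4, so 40-47% do not, although all benefit equally.
- With no effect at all, 26-41% still fall by at least 0.4.
- Change correlates −0.23 to −0.42 with baseline. Squared, that is about 5-18% of the variance of change.

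Over a wider range (SD 0.8-1.2, r 0.5-0.9) the gap between thirds runs from 0.12 to 0.93. For comparison, Table 2 takes 0.3 points as clinically meaningful.

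**3. What the control arm does to this.** The same gap arises in the control group. At m = 8.0 and r = 0.5 the top third falls 0.69 more than the bottom third in each arm, and 0.69 − 0.69 = 0, which is the true difference in effect.

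**4. Precision of the both-arm analysis.** Take a baseline characteristic that splits patients 50/50, SD = √((0.8² + 1.0²)/2) = 0.9055, and SE of the interaction = SD × √(4/(n/2)) for n per arm.

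- n = 61: SE = 0.9055 × √(4/30.5) = 0.328. For a 0.4-point interaction, 0.4/0.328 = 1.22 and power is Φ(1.22 − 1.96), about 23%. The interaction detectable with 80% power is 2.80 × 0.328 = 0.92.
- n = 77: SE = 0.9055 × √(4/38.5) = 0.292. Power is Φ(1.37 − 1.96), about 28%. The interaction detectable with 80% power is 0.82.
- Total for 80% power: 16 × 0.82 × 2.80² / 0.4², about 644 analysed patients.

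These figures give no credit for baseline adjustment. If 0.9055 is the SD of HbA1c itself, adjustment multiplies the SE by about √(1 − r²). At r = 0.8 that is 0.6, and with 77 per arm the SE is 0.175 and power is Φ(2.28 − 1.96), about 63%. Even this favourable case stays below 80%.

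**The case against.** The strongest reply is that the row does not state a single-arm analysis. The primary endpoint row uses similar shorthand, naming change during app use with no comparator, yet the analysis section compares it between arms. Leaving the control group out of a row therefore does not prove that its data go unused. This stands: a reader might infer that the plan ignores the control group here, but the wording is ambiguous.

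Three further inferences are tempting and also unsupported:

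- **That regression to the mean is the main thing the endpoint would pick up.** Baseline-driven regression explains only about 5-18% of the variance of change in the illustration. The gaps in the table also concern thirds of baseline HbA1c. The row names SDSCA and DES-SF, and groups formed on those scores inherit such a gap only so far as the scores track baseline HbA1c, which the documents do not quantify. For them, mistaking prognosis for effect is the larger risk.
- **That the Pearson correlation is the method for this endpoint.** The sentence is not tied to it.
- **That the endpoint will decide who is offered the app.** No section says so. The Discussion ties classification of the app to its effect against standard care.

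One may also say that modelling of effect modifiers belongs in a statistical analysis plan, which is not shown. The missing interaction model alone would indeed be no finding. The definition, however, is stated text: the explanatory clause makes effect mean size of change, and an analysis plan that followed it faithfully would carry the error forward.

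**Conclusion.** The point holds in limited form. The row equates effect with observed change and states no contrast with the control group, and the analysis section names no interaction other than treatment by visit. Followed as written, it can yield apparent responders and non-responders with no true difference in effect: about 0.3 to 0.8 points between baseline-HbA1c thirds, and 40-47% of patients short of a 0.4 fall. Both figures rest on the assumed mean, SD and correlation; the documents give no baseline-to-follow-up correlation. Regression to the mean is one contributor among several.

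Nor should a reader infer that an interaction analysis would settle who benefits. It targets the right quantity, but at this trial's size it can only be exploratory. The point concerns one secondary endpoint and leaves the primary comparison untouched. It should be corrected before analysis.

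**What to change.** Redefine the endpoint as the difference in treatment effect across prespecified baseline characteristics, for example baseline HbA1c, Visit 1 SDSCA and DES-SF scores, diabetes type and age. Estimate it in both arms from a model of Visit 3 HbA1c with treatment, baseline HbA1c, the characteristic, and treatment by characteristic. Where the characteristic is baseline HbA1c itself, the model has treatment, baseline HbA1c and their product. Use baseline scores only, since later scores may themselves be changed by the app.

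Report each interaction estimate with its 95% confidence interval and label the set exploratory. State that patients or groups will not be described as benefiting or not benefiting on observed change alone.

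The cost is a reworded table row and a small amount of analysis. HbA1c is already measured in both arms at every visit, and the example characteristics need no additional visit. The price is wide intervals, which is why the exploratory label is needed.
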